
### Recruitment, randomisation, blinding and non-blinding

Advertisements for the study will be posted at the Catholic Kwandong University International St. Mary’s Hospital using banner advertisements and posters. We also plan to post the advertisements on the hospital home page, in the monthly hospital magazine, at the internet café and on the subway at least five times. All these advertisements will be done with the approval of the IRB.

After recruitment, patients will be randomised to one of the four trial arms. Randomisation will be performed using a list of block randomisations made by statisticians, independent of this clinical trial. A researcher who is not involved in the process of drug prescription and evaluation will execute the randomisation process.

During the treatment period, the patients and all researchers (investigators and CRCs) will be blinded, except the researchers who conducted the randomisation procedure. In addition, the researchers will not know the kind of medication that is being administered to the patient or any other information that could lead to bias.

Allocation concealment will be performed during the process of medication administration. The management pharmacist, who will not be involved in analysing the results of the trial, will use the randomisation table to label the medication with the assignment number and provide the medication. The patients will take the drugs contained in the opaque envelope, which will be labelled with the assignment number.

Non-blinding will be performed only in the following situations: (1) if the trial is terminated and there is a need for statistical analysis; (2) if a serious medical emergency occurs and information about the medication is needed and (3) if the chief investigator determines that non-blinding is necessary.

The entire process of the study will be directed by the authorised clinical research organisation (CRO), DreamCIS, Seoul, Korea.

### Intervention

The herbal formula SRS is commonly used by Korean traditional medical doctors for the treatment of diarrhoea and related diseases.^13–18^ SRS used in this study (Samryungbaekchulsan granule; Han Kook Shin Yak, Nonsan, South Korea) is extracted with water and mixed with starch and lactose in accordance with Korean Good Manufacturing Practice. Production of SRS is regulated and allowed by the KMFDS. SRS contains 10 herbs, listed in table 1. Placebo-SRS is made from cornstarch and has the same taste, shape, colour and similar scent as SRS. SRS and placebo-SRS will be sealed in identical aluminium bags with the same labelling. These herbal drug packages will be distributed by an independent pharmacist in an isolated room. According to the recommended dosing methods of KMFDS, after SRS or placebo-SRS is dissolved in boiled water, the subjects will take them 30 min before each meal (5 g/pack, three times a day).

**Table 1 T1:** Ingredients in the herbal formula Samryungbaekchulsan

Scientific name	Part used	Grams per day
Atractylodes rhizoma Alba	Root	3.0
Poria sclerotium	Dried core	4.0
Dioscoreae rhizoma	Root	3.0
Glycyrrhizae radix et rhizoma	Root	1.5
Coicis semen	Seed	8.0
Nelumbinis semen	Fruit	4.0
Platycodonis radix	Root	2.5
Dolichoris semen	Seed	4.0
Amomi fructus	Fruit	2.0
Ginseng radix	Root	3.0

OB (Menoctyl Tab; Dong Hwa Pharm, Seoul, Korea) is a tablet containing OB 40 mg. Placebo-OB is a tablet made of Ludipress with the same taste, shape and colour as OB. Patients will be instructed to swallow one tablet of OB or placebo-OB 30 min before each meal over the administration period. The drugs used in the trial (SRS, OB, placebo-SRS, placebo-OB) have been approved by the KMFDS. Patients will be asked at the end of the study whether the drugs that they have been taking are either real or placebo, to measure the success of blinding. Compliance will be confirmed by counting returned SRS packets or OB tablets. Every patient will be instructed to write down any adverse events during the administration period, and these records will be evaluated at the follow-up. At the patient visits (at 0, 4 and 8 weeks), we will perform a check of vital signs, physical examination, ECG and laboratory tests to evaluate safety for the patients. All side effects will be reported to the investigator.

### Rescue therapy and concomitant medications

Participants are prohibited from taking any medication that could affect D-IBS during the entire course of the trial. However, if serious side effects occur or symptoms worsen, investigators will provide quick and appropriate treatment (including drug administration), based on their medical judgement. In this case, the direct investigators will record the treatment or drug administration and report to the IRB within 24 hours to determine whether the trial should be continued or discontinued.

### Outcome measurements

#### Primary outcome

The primary outcome will be measured via a questionnaire that confirms subjective symptom improvement. Participants will respond a total of five times during and after the administration period (at 2 and 6 weeks via telephone, and at 4, 8 and 12 weeks during direct visits) to the following question: Subject’s Global Assessment of Relief—‘How much do you think the symptoms of D-IBS have improved compared to before the clinical trial?’ According to the answers given by the patients to this survey, the improvement is given a score of 0, 1, 2, 3 or 4.

#### Secondary outcomes

At 2, 4, 6, 8 and 12 weeks from the start of the treatment period, patients will be assessed for severity of D-IBS symptoms (abdominal pain, abdominal discomfort, satisfaction of defecation, frequency of abdominal pain, quality of life) using a Likert scale ranging from 0 to 10.^31^ Patients will also be instructed to record the number of defecations per day, BSF and the degree of force used in bowel movements at 0, 2, 4, 6, 8 and 12 weeks.^32^

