### Design

This study is a placebo-controlled, double-blind trial. Eighty patients will be enrolled and randomly assigned to four separate arms of the trial. The trial will be conducted at Catholic Kwandong University International St. Mary’s Hospital, Incheon, South Korea.

The study subjects will be required to participate in a 2-week preparation period (weeks −2 to 0) and an 8-week drug-administration period (weeks 0–8). The patients will visit four times, on weeks 0, 4, 8 and 12. The primary outcome measurement will be evaluated at weeks 2, 4, 6, 8 and 12, and the secondary outcome measurement will be evaluated at weeks 0, 2, 4, 6, 8 and 12. Participants will be assessed for efficacy and safety of the treatment through visits (0, 4, 8 and 12 weeks) and telephone questionnaires (2 and 6 weeks). In addition, laboratory tests will be conducted at 0, 4 and 8 weeks. According to the intervention protocols, the clinical research coordinator (CRC) will encourage patients and participants to complete follow-up at every visit.

During the drug-administration period, SRS or its placebo will be given as one pack of water extract granules three times a day, 30 min before each meal. OB or its placebo will be given as one tablet three times a day, 30 min before each meal.

Participants will be divided into four groups: (1) SRS and OB group, (2) SRS and placebo-OB group, (3) placebo-SRS and OB group and (4) placebo-SRS and placebo-OB group. The entire flow chart of the study is shown in figure 1.

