### Sample size calculation

This trial is a study for a new therapeutic regimen of SRS and OB combination treatment. In a similar study conducted previously by using coadministration of a probiotics mixture and an herbal medicine (placebo-controlled, double-blind and randomly four-arm trial), each arm consisted of at least 15 patients, and the total sample size was more than 60 participants.^27^ In other similar studies, clinical trials have been conducted with a total of 60–64 participants, consisting of 12–30 patients per group.^28–30^ Based on these previous studies, the minimal clinical significance of the trial can be obtained when only 16 participants complete the trial. Because the dropout rate is expected to be 20%, each trial group will be made up of at least 20 participants. Therefore, the total sample size must be more than 80 participants.

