### Inclusion criteria

The following patients would be included: (1) patients aged 18–75 years; (2) patients satisfying the Rome III criteria of IBS (recurrent abdominal pain or discomfort that began at least 6 months before the clinical trial, with a rating of more than 3 on a 10-point scale, frequency of at least 3 days/month in the last 3 months and associated with two or more of the following: improvement associated with defecation, onset associated with a change in frequency of stools and onset associated with a change in form of stool)^1 9^; (3) patients satisfying the Rome III criteria of IBS, whereby D-IBS type is defined as loose/mushy or watery stools—Bristol Stool Form (BSF) Scale 6–7 ≥2 times/week^1 30^; (4) patients with a negative urine pregnancy test (in women of a childbearing age, within 7 days before the clinical trial) and who consent to using contraception during the administration period; (5) patients with the ability to read the symptom questionnaire and understand it and (6) patients who agree with the clinical plan and voluntarily sign the institutional review board (IRB)-approved documents.

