#### Statistical analysis

The statistical analysis will be conducted by blinded professional statisticians. To evaluate the efficacy of the study, both an intent-to-treat (ITT) analysis (primary analytical method) and a per-protocol (PP) analysis (secondary analytical method) will be performed. The ITT analysis will be conducted for all patients who were followed up at least once after randomisation and will be able to be evaluated for effectiveness. The PP analysis will be performed for patients who complete the 8-week treatment course and meet the inclusion and exclusion criteria.

To analyse the continuous variables in the demographic information and pretreatment characteristics between groups, a one-way analysis of variance (ANOVA) and Kruskal-Wallis test will be conducted. An ANOVA and Kruskal-Wallis test will also be used to test for symptom improvement compared with baseline (0 week) and the variables for analysis that include the following: (1) subjective symptom improvement (primary outcomes) and (2) severity of symptoms related to D-IBS (abdominal pain, abdominal discomfort, satisfaction of defecation, frequency of abdominal pain and quality of life). All values will be shown as mean±SEM. Comparisons of outcome assessments between the four groups will be performed using the paired t-test or Wilcoxon signed-rank test.

If the Subject’s Global Assessment of Relief on the Likert scale is ‘0’ or ‘1’ for more than 2 weeks between weeks 8 and 12, then the symptoms will be considered to have improved sufficiently. Based on this, we will calculate the symptom relief rate by dividing the number of participants who exhibited sufficient symptom relief by the total number of participants in the trial and present descriptive statistics. The CATMOD procedure will be used to evaluate the improvement of symptoms compared with baseline. Comparisons between the four groups will be conducted using the χ^2^ test or Fisher’s exact test. These statistical analyses will also be performed at 2, 4, 6, 8 and 10 weeks from baseline. The Cochran-Mantel-Haenszel test will be used to confirm the difference between the intervention groups at each time point.

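### The severity schedule omits the week-0 score that the analysis compares against, and the named ANOVA does not adjust for that score

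*Protocol article*

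**What the plan says.** Three sections of the protocol article bear on this.

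- **Design**: "the secondary outcome measurement will be evaluated at weeks 0, 2, 4, 6, 8 and 12". Week 0 is included, without distinction between the secondary measures.
- **Secondary outcomes** sets the times for the five scales: "At 2, 4, 6, 8 and 12 weeks from the start of the treatment period, patients will be assessed for severity of D-IBS symptoms". Week 0 is absent. The next sentence, on defecation count, stool form and straining, does include it: "force used in bowel movements at 0, 2, 4, 6, 8 and 12 weeks".
- **Statistical analysis**: "An ANOVA and Kruskal-Wallis test will also be used to test for symptom improvement compared with baseline (0 week", and among the variables it lists "severity of symptoms related to D-IBS (abdominal pain, abdominal discomfort, satisfaction of defecation, frequency of abdominal pain and quality of life". These are the same five items. No baseline covariate is named.

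The abstract also counts change in symptoms among the secondary outcomes.

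**The concern.** There are two linked problems.

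The first is the schedule. Two neighbouring sentences in Secondary outcomes differ only in whether week 0 is listed, so staff working from that section could take the omission for the severity scales as intended. A severity score not taken before treatment cannot be obtained later. Trial status reports the first randomisation on 29 March 2016 and recruitment still under way, so the answer already matters for enrolled patients.

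The second is the analysis. If improvement from week 0 is computed as a change score, the baseline is subtracted with a fixed coefficient of 1, whatever its actual relation to the follow-up score. ANCOVA estimates that coefficient from the data. In a trial with 20 patients per arm, any precision available from a score already on file is worth having.

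**Working it through.** **The plan's own figure.** Sample size calculation states "the minimal clinical significance of the trial can be obtained when only 16 participants complete the trial", with 20% dropout. Read per group, 16 / (1 − 0.20) = 20, and 4 × 20 = 80. This reproduces the stated size and does not depend on the present point. The article gives no effect size, SD, baseline correlation or power, so everything below rests on assumed values.

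**Can the planned comparison be computed?**

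| Section | Week 0 for the five severity items? |
|---|---|
| Design | Yes |
| Secondary outcomes | No (yes for the bowel records) |
| Statistical analysis | Required, as the reference point |

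If Secondary outcomes is literally right, improvement from week 0 has no starting value for any of the five items. If Design is right, it can be computed.

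**Precision when week 0 is available.** Set the follow-up SD to 1, the baseline SD to k and the baseline-to-follow-up correlation to r.

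- Var(change) = 1 + k² − 2rk
- Var(ANCOVA) = 1 − r²
- Difference = (k − r)², which is never negative (ignoring the one degree of freedom spent on the covariate)

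With k = 1 the ratio Var(ANCOVA)/Var(change) reduces to (1 + r)/2. The case k = 0.7 is an illustration of a narrower spread at baseline.

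| r (assumed) | k (assumed) | Var(change) | Var(ANCOVA) | Ratio | Equivalent extra patients (1/ratio − 1) |
|---|---|---|---|---|---|
| 0.3 | 1 | 1.40 | 0.91 | 0.65 | 54% |
| 0.5 | 1 | 1.00 | 0.75 | 0.75 | 33% |
| 0.7 | 1 | 0.60 | 0.51 | 0.85 | 18% |
| 0.3 | 0.7 | 1.07 | 0.91 | 0.85 | 18% |
| 0.5 | 0.7 | 0.79 | 0.75 | 0.95 | 5% |
| 0.7 | 0.7 | 0.51 | 0.51 | 1.00 | 0% |

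**What this means for power.** Take 16 completers per group, two-sided 0.05 and an illustrative pairwise difference of 0.8 follow-up SDs. Power ≈ Φ(0.8 / √(variance × 2/16) − 1.96).

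| r | Change score, k = 1 | Change score, k = 0.7 | ANCOVA |
|---|---|---|---|
| 0.3 | 48% | 59% | 66% |
| 0.5 | 62% | 72% | 74% |
| 0.7 | 83% | 89% | 89% |

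**If week 0 was not collected.** The follow-up scores alone can still be compared between arms. Their variance is 1.00 on this scale, against 1.40 for the change score at r = 0.3 and k = 1, and equal to it at r = 0.5.

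**The case against.** The strongest reply is that one sentence is out of line with two others. A week-0 visit exists, Design assigns secondary outcomes to it, and Statistical analysis names week 0 as baseline. That stands: an omission in Secondary outcomes is the likelier explanation. A reader might infer that the severity analysis is impossible; the documents support that only if the outlying sentence is followed to the letter. The eligibility criterion, "with a rating of more than 3 on a 10-point scale", shows that some pre-treatment rating of pain or discomfort exists. However, it is not stated to be the outcome item and says nothing about satisfaction with defecation or quality of life.

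A reader might also infer that the plan ignores the baseline, or that chance imbalance biases it. Neither holds. A change score uses the baseline, with a fixed weight, and under randomisation it gives an unbiased comparison and a valid test. The loss is one of efficiency.

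Nor is the size of the loss settled. Equal SDs are an assumption, and the entry threshold may narrow the baseline spread for pain and discomfort, which is why the k = 0.7 rows are shown. The variance formula does not cover the Kruskal-Wallis test. Analysing change scores is itself the natural reading rather than the literal wording: the same sentence also covers the global relief score, which has no week-0 value. An unseen analysis plan may name a covariate, but the protocol does fix ANOVA and Kruskal-Wallis without one.

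Finally, a reader might infer that stool frequency and form have no planned analysis because they are not listed with the severity items. The list is introduced as inclusive and the article is condensed, so this is not supported.

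The same section also says "Comparisons of outcome assessments between the four groups will be performed using the paired t-test or Wilcoxon signed-rank test". Those are within-patient tests, and their use for comparing arms is a separate matter.

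**Conclusion.** The schedule conflict is established from the text and needs correction. Its worst consequence, five scales with no baseline, is possible but not the likelier case, and even then a randomised comparison of follow-up scores would survive.

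The analysis point holds as a matter of efficiency. In large samples ANCOVA is never less precise than the change score, and over the assumed range (r from 0.3 to 0.7, k of 1 or 0.7) it has between 65% and 100% of the change-score variance. Neither r nor k is in the documents, so no single gain can be claimed. The primary outcome and the stated sample size are unaffected.

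**What to change.** 1. In Secondary outcomes, add week 0 to the schedule for the five severity scales, so that it agrees with Design and Statistical analysis.
2. Confirm that the week-0 scores were collected for every patient already randomised, and report any that are missing. This cannot be repaired afterwards.
3. In Statistical analysis, specify ANCOVA on the week-8 severity score with the week-0 score as covariate, or a repeated-measures model with the same covariate. Keep Kruskal-Wallis as a sensitivity analysis.
4. Optionally, use the same model for stool frequency and form, whose week-0 values are already scheduled.

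The cost is wording and, if the scales are not already given at week 0, one short questionnaire at an existing visit for patients still to be enrolled. No extra patients are needed.

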#### Safety assessments

The investigator will record all adverse events that occur during the trial along with any concomitant medications in the case reports. When an adverse event occurs, the investigator will record the symptoms and signs of the adverse reaction, the duration (start and end date), severity, course, outcome, significance, causality by the trial drug and any action taken in relation to the adverse event. In the case of concomitant medicines, composition, dosage, duration of administration and reason for medication will be recorded in detail. Symptoms that existed before the start of the clinical trial will not be recorded as adverse events.

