### Hypothesis

We hypothesise: (1) that coadministration of SRS and OB will have a more positive effect on D-IBS symptoms than either SRS or OB alone; (2) that after 8 weeks of treatment with SRS, OB or both drugs, the Subject’s Global Assessment of Relief and severity of D-IBS symptoms will be more improved than after treatment with placebo and (3) that coadministration of SRS and OB will be safe for patients with D-IBS.

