A statistical analysis will also be conducted to evaluate safety. The incidence of adverse events and abnormality of experimental results will be analysed statistically according to the groups, and non-parametric methods will be applied as necessary using a paired t-test for continuous data, McNemar’s test for categorical data, Fisher’s exact test for adverse events and a generalised estimating equation for clinically significant changes between groups.

All statistical analyses will be conducted using SAS software, V.9.1.3 (SAS institute). A P value <0.05 will be considered statistically significant.

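### Read literally, the rule on pre-existing symptoms keeps on-treatment worsening of loose stools and abdominal pain or discomfort out of the adverse-event count

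*Protocol article*

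**What the plan says.** The Safety assessments section of the Protocol article opens with a broad duty: "The investigator will record all adverse events that occur during the trial along with any concomitant medications in the case reports". For each event the investigator documents, among other things, dates, severity, outcome, causality and action taken. The section closes with an exclusion: "Symptoms that existed before the start of the clinical trial will not be recorded as adverse events". Nothing there or elsewhere in the article says how to treat such a symptom if it gets worse on treatment.

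Under Inclusion criteria, every participant must have a history of 6 months or more of abdominal pain or discomfort, "with a rating of more than 3 on a 10-point scale". For the subtype, "D-IBS type is defined as loose/mushy or watery stools", with Bristol types 6–7 at least twice a week.

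The third item under Hypothesis is "that coadministration of SRS and OB will be safe for patients with D-IBS". The safety part of Statistical analysis states: "The incidence of adverse events and abnormality of experimental results will be analysed statistically according to the groups", and names Fisher's exact test for adverse events.

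Deterioration is foreseen in Rescue therapy and concomitant medications: "if serious side effects occur or symptoms worsen, investigators will provide quick and appropriate treatment". That treatment is recorded and reported to the ethics board within 24 hours. The section does not say whether the deterioration is an adverse event.

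**The concern.** The exclusion depends only on whether the symptom was present before the trial. It makes no exception for a symptom that becomes more severe, more frequent or serious. The symptoms it covers are the entry criteria themselves, so it bears on all participants and not on a few with incidental complaints.

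Both products act on the gut. If either of them, or the combination, aggravates stools, pain or discomfort in some participants, an investigator who follows the sentence as written would not enter that as an adverse event. The between-arm comparison of adverse-event incidence, which is one of the main supports for the safety hypothesis, would then miss it. An analysis plan could not restore the missing entries, because the information is lost when the data are recorded.

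**Working it through.** The point concerns a recording rule, so the main check is to follow one case through the sections.

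1. **Who is covered.** Entry requires loose or watery stools in everyone, and pain *or* discomfort in everyone. Worsened loose stools therefore fall under the exclusion in every participant. Worsened pain does so only in those who had pain at entry, and likewise for discomfort. New pain in a participant who entered with discomfort alone would be recordable.
2. **What happens to a worsened entry symptom.** Under the literal rule in Safety assessments it is not an adverse event. It then gets no causality, severity, outcome or action-taken entry as one, and does not enter the incidence compared in Statistical analysis.
3. **Where it can still appear.** Secondary outcomes provides 0 to 10 scales for pain, discomfort and pain frequency at weeks 2, 4, 6, 8 and 12. It also provides stool frequency and form at weeks 0, 2, 4, 6, 8 and 12. Treatment given for worsening is recorded and reported under the rescue section. These are efficacy or management data, and outcome values are to be shown as mean±SEM, so a group mean can improve while individuals deteriorate.

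**Denominator.** The article's own size reproduces: 16 / (1 − 0.20) = 20 per arm, and 4 × 20 = 80. The point does not depend on this figure.

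**Scale, by assumption only.** The article gives no worsening rate. For an assumed rate p, the expected number of participants who worsen is 20p per arm and 80p overall. The chance of at least one in an arm is 1 − (1 − p)^20.

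| Assumed p | Expected per arm of 20 | Expected in 80 | Chance of at least one in an arm | Counted under the literal rule |
|---|---|---|---|---|
| 5% | 1 | 4 | 0.642 | 0 |
| 10% | 2 | 8 | 0.878 | 0 |
| 20% | 4 | 16 | 0.988 | 0 |
| 30% | 6 | 24 | 0.999 | 0 |

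**An assumed contrast.** With 20% on the combination and 5% on placebo, 4/20 v 1/20 would be reported as 0/20 v 0/20. With 5 events among 40, the probability of 4 in the combination arm is C(20,4)·C(20,1)/C(40,5) = 96,900/658,008 = 0.147. The probability of 5 is C(20,5)/C(40,5) = 15,504/658,008 = 0.024. The upper tail is 0.171 and, the arms being equal in size, the two-sided Fisher p is about 0.34. Restoring the events would not give a significant difference at this size. What changes is the table a reader sees.

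**The case against.** The best case for the plan has five parts.

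- **The sentence may mean unchanged symptoms only.** A deterioration that begins on treatment is arguably a new event, and the opening sentence asks for all adverse events. This reading is possible, but the text does not state it, and two investigators could apply the rule differently.
- **There is a fallback.** Data collection, access and management sends unspecified matters to the ICH and Korean good clinical practice guidelines. But the handling of pre-existing symptoms is specified, and without an exception, so the fallback does not clearly reach it.
- **This is a condensed article.** The full protocol may contain a clause on worsening. If so, the article's sentence only needs to be aligned with it. Still, the article is not silent here: it states a rule, and that rule omits the exception.
- **Safety does not rest on adverse events alone.** The Discussion names periodic assessment of subjective symptoms, physical measurements and laboratory tests. Statistical analysis adds abnormal results and a generalised estimating equation for clinically significant changes. This stands. It limits the loss to one strand of the safety evidence, although Laboratory tests says that no detailed statistical analysis is planned there.
- **Worsened diarrhoea may not be the likeliest harm.** The article describes both products as reducing gut motility, and harm in the opposite direction is not an entry symptom and would be recorded. This also stands: the article does not establish that aggravation is likely or differs by arm. It does not exclude it either. The SRS granule contains lactose, its placebo is described as made from cornstarch, and lactose intolerance is an exclusion only when diet does not control it.

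**Conclusion.** The point holds for the adverse-event count under the literal reading of the rule. Worsening of symptoms that the entry criteria require is left out of the incidence compared between arms and is not characterised as an adverse event. Any resulting error makes treatment look safer on that count. Its size is unknown: the figure of 1 to 6 participants per arm rests wholly on assumed rates of 5% to 30%.

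Three stronger conclusions that a reader might draw are not supported.

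- Drug-induced worsening does not vanish from the trial, since the symptom scales, stool records and rescue reports can still show it. Nor is a difference between arms impossible to see.
- A zero count is not certain in practice, because some investigators may read the sentence as covering unchanged symptoms only.
- Not every participant has abdominal pain at entry; discomfort suffices.

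**What to change.** Amend the last sentence of Safety assessments along these lines: *a symptom present before the first dose is recorded as baseline and is not an adverse event unless it worsens in severity, frequency or seriousness after the first dose; the worsening is then recorded as an adverse event.* Three changes go with it.

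- Reconcile the sentence with Rescue therapy and concomitant medications, so that it is clear whether worsening that leads to treatment is also an adverse-event entry. This concerns recording only, not how participants are managed.
- Fix the reference point at week 0. Design places the secondary outcomes at week 0 and Statistical analysis compares with week 0, but Secondary outcomes lists the severity scales only from week 2. These need to agree, or worsening has no stated baseline on those scales.
- Tabulate worsening of pre-existing gastrointestinal symptoms by arm.

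The cost is a one-sentence amendment and case-report-form guidance. It will bring more adverse-event entries, including natural fluctuation of the disease, which should fall on all arms alike under blinding, and some overlap with efficacy endpoints. Trial status reports that recruitment was ongoing. For participants already treated, worsening could be partly reconstructed from the rescue reports, symptom scales and stool records.
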